### Data collection and management

The outcome assessors will use the CRFs to collect the data which consists of a questionnaire-based assessment of treatment effects, active range of motion (AROM), tissue hardness, adverse events, and safety evaluations. Then, two data administrators who do not belong to the research team and blinded to group allocation will independently receive the completed CRF and enter it into the Excel database (Microsoft, Redmond, WA, USA). They must complete rigorous data monitoring training. Then, they enter the real-time data into the China Clinical Trial Registry (http://www.chictr.org.cn), where the electronic data management system will be used for real-time tracking and monitoring of test data from the Science and Technology Department of Yueyang Hospital.

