**Methods/design:**

A randomized controlled trial in which 102 patients with non-specific chronic neck pain will be recruited and randomly allocated to either the Tuina group or the Yijinjng combined with Tuina group in a 1:1 ratio. The interventions for both groups will be carried out three times a week for 8 weeks. The patients in the two groups will receive follow-up 1 month after the intervention. The primary outcome will be the changes in the visual analog scale (VAS). Secondary outcomes will be measured by the Neck Disability Index (NDI), Self-Rating Anxiety Scale (SAS), and Tissue Hardness and Active Range of Motion (AROM). The data will be analyzed at the baseline, 4 weeks during the intervention, at the end of the intervention, and 1 month after the intervention. The significance level sets as 5%. The safety of interventions will be evaluated after each treatment session.

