## Methods/design

### Study design

This present study is a single-center, randomized, and analyst-blinded controlled trial with two arms: Tuina group (control) and Yijinjng combined with Tuina group (intervention). The study protocol has been approved by the Regional Ethics Review Committee of Yueyang Hospital of Integrated Traditional Chinese and Western Medicine affiliated with Shanghai University of Traditional Chinese Medicine (project number: 2020-018). A total of 102 eligible NCNP patients will be recruited and assigned in a 1:1 ratio randomly. Written informed consent will be provided by all patients. Independent researchers who are blinded to the patient assignment will collect and analyze the outcome assessment and related data. The study design is illustrated in the flow chart in Fig. 1. The main treatment center will be the Shanghai University of Traditional Chinese Medicine.

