### Blinding

Patients will be informed of the type of treatment that they will receive. The therapists will know the allocation so they should learn how to communicate with patients to ensure treatment blinding. In order to reduce the risk of bias, evaluators, data managers, and statisticians will be unaware of the group assignments in the result evaluation procedures and data analysis. The blinding procedure will be operated until the data are locked.

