### Safety evaluation

The safety of patients will be monitored in every visit. Two attending physicians and two responsible spine care specialists will be responsible for the collaboration and guidance of clinicians during each clinical trial and implementation. The two chief spinal surgeons constitute the endpoints Adjudication Committee, which is responsible for the overall supervision of the clinical trials. The AES in trial are changes in pain, syncope, vertigo, and disability. For any AES, no matter if it is or not caused by intervention, the treatment will be stopped immediately. The patient should take any medical aids to alleviate symptoms. The adverse events should be reported to the relevant responsible unit and the ethics committee in time. If the adverse events are confirmed to be related to the study, the regional Ethics Review Committee of Yueyang Integrated Traditional Chinese and Western Medicine Hospital affiliated to Shanghai University of Traditional Chinese Medicine has the right to suspend the study. If an adverse event occurs during the clinical trial, medical experts will be engaged to assess and investigate the actual cause, and medical and financial compensation will be made to participants.

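### Giving adverse event and safety recording to the blinded outcome assessors puts evaluator blinding at risk for tissue hardness and, in part, for AROM

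*Protocol article*

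**What the plan says.** All references are to the protocol article.

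- **Data collection and management** gives one role both tasks. "The outcome assessors will use the CRFs to collect the data which consists of a questionnaire-based assessment of treatment effects", and the list goes on through AROM to "tissue hardness, adverse events, and safety evaluations".
- **Abstract, Methods/design**, on timing: "The safety of interventions will be evaluated after each treatment session". **Safety evaluation** adds: "The safety of patients will be monitored in every visit".
- **Study design**, on who is blinded: "Independent researchers who are blinded to the patient assignment will collect and analyze the outcome assessment and related data". **Blinding** says that "evaluators, data managers, and statisticians will be unaware of the group assignments in the result evaluation procedures and data analysis", with blinding kept until data lock. **Objectives** describes the trial as evaluator- and statistician-blinded.
- **Blinding** also says that patients are told which treatment they get. Its one instruction on communication is addressed to the therapists.
- **Safety evaluation** names other staff: "Two attending physicians and two responsible spine care specialists will be responsible for the collaboration and guidance of clinicians". It does not say who questions the patient or completes the form.

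**The concern.** Evaluator blinding is a design property that the article claims for itself, and a reader will rely on it when judging the results. It can do little for VAS, NDI and SAS, which unblinded patients complete themselves. Its main work is on the two outcomes that a member of staff measures: tissue hardness and AROM.

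The person who takes those measurements is also told to collect safety data. To record an adverse event one normally asks what happened and when. In the combined arm the honest answer may be that it happened during Yijinjing, and only that arm does Yijinjing. At stake is whether the between-arm comparisons of tissue hardness and AROM can fairly be reported as made by someone unaware of allocation. Strengths and limitation of the study concedes that therapists and patients are unblinded and that self-report is open to expectation, but does not mention this route.

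**Working it through.** The article gives no figure for this point, so there is nothing to reproduce. The check sets the sections side by side and counts contacts from the stated schedule.

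**1. Do the two tasks fall to the same role?** Yes. Data collection and management names the outcome assessors once and lists efficacy and safety items together. No other section gives the collection of adverse events to anyone else.

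**2. What differs between the arms?** Only Yijinjing. The Tuina steps are the same in both arms (Yijinjing combined with Tuina group).

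**3. Count of contacts per patient (Interventions; Outcome measurements).**

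| Contact | Arithmetic | Number | Arm |
|---|---|---|---|
| Tuina sessions | 3 per week × 8 weeks | 24 | both |
| Supervised Yijinjing classes | 1 per week × 8 weeks | 8 | combined only |
| Home Yijinjing practices | 2 per week × 8 weeks | 16 | combined only |
| Outcome assessments | weeks 0, 4, 8, 12 | 4 | both |

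The combined arm thus has 8 + 16 = 24 exercise sessions from which an arm-specific event could be reported; the Tuina arm has none. Allocation follows the baseline assessment (Randomization and allocation concealment), so 4 − 1 = 3 assessments can be affected by knowledge of the arm.

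**4. Two readings of when assessors collect safety data.**

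- *Only at the assessment visits.* Safety information is taken at weeks 4, 8 and 12, around the time of measurement. That is 3 occasions per patient.
- *After every session as well.* There would be at least 24 contacts per patient. This is an outer case. No section assigns the post-session check to the assessors, and a check after Tuina does not by itself show the arm.

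The risk is present under both readings; only the number of occasions changes.

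**5. Which outcomes can an informed assessor influence?**

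- *VAS, NDI, SAS:* completed by patients who know their arm. Assessor blinding does not protect them, and its loss does not harm them further in any way the text shows.
- *Tissue hardness:* the researcher places the meter, controls the push and reads the value. This is the most exposed outcome.
- *AROM:* the researcher instructs the patient and starts and ends the recording, but the patient decides when pain stops the movement and the computer stores the value. It is exposed in part, and it already depends on an unblinded patient.

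**6. Is a safeguard stated?** None. No section separates safety recording from measurement, and none asks patients to keep their treatment from the assessor.

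The possible bias cannot be put in numbers. The article gives no expected difference or variability for tissue hardness or AROM, and no estimate of how often assessors would be unblinded.

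**The case against.** A reader might infer that the assessors are bound to learn the allocation, that evaluator blinding therefore fails, and that each patient brings 24 unblinding contacts. The article does not support this. The sentence on post-session evaluation names no role. No section places assessors at the sessions or the class. The 24 Tuina sessions have the same content in both arms. Home-practice videos go to the Yijinjing teacher. The listed adverse events are not specific to exercise. Assessors could record events at the scheduled visits, or from clinicians' reports, without contradicting any sentence. All of this stands, and it limits the point to a risk.

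Four further arguments deserve an answer.

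- *An unblinded patient may mention Yijinjing to any assessor, whoever records safety.* True, and this is a general limit of such trials. But questions about adverse events prompt disclosure, and here the plan itself assigns those questions to the assessor.
- *This is operational detail that a condensed article leaves out.* That would hold if the article were silent. It is not: it allocates the task, and allocates it to the blinded role.
- *Tissue hardness is standardised.* The meter is held perpendicular, the push ends at a sound, the researchers practise for a week, and three readings are averaged. These steps reduce operator variation but do not remove the operator's influence on each reading.
- *Blinded recording of adverse events is itself defensible*, since Statistical analysis compares adverse effects between arms. This stands as a real trade-off and is carried into the fix.

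**Conclusion.** The point holds as a risk to a stated design property. The article gives safety recording to the blinded assessors, leaves patients aware of an intervention found in one arm only, and states no safeguard. Evaluator blinding is therefore endangered for tissue hardness, and in part for AROM, on at least the three post-randomisation assessments.

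It does not reach the primary outcome, the sample size or the primary conclusion, and the documents do not show that blinding must fail. The conclusion rests on two assumptions: that the assessors carry out the safety collection as Data collection and management is written, and that at least some of it involves talking to the patient. If they only transcribe clinicians' records, the route narrows to what those records disclose. The change is worth making because it is cheap and it protects the outcomes for which evaluator blinding does most.

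**What to change.** 1. In Data collection and management, remove adverse events and safety evaluations from the outcome assessors' task, leaving the questionnaires, AROM and tissue hardness.
2. In Safety evaluation, state which clinical staff already in the protocol make the safety record after sessions and at visits. Have them use a separate form that is withheld from the assessors. The physicians and specialists named there now have a guiding role only, so the task has to be assigned expressly.
3. In Blinding, add that patients are asked not to mention their treatment at the week 4, 8 and 12 assessments.

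The cost is one additional form, one reassigned task and a short instruction to patients. Treatment, safety rules, schedule and sample size are unchanged. The downside is that adverse events, which are compared between arms, would be recorded by staff who may know the arm, so ascertainment could differ. State this as a limitation.

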### Quality control

Quality control will be conducted during the study. The head of research center will be responsible for the coordination, development, and quality control of all the programs in the trial. During the trial, the reviewers who are independent of the researcher and sponsor will extract 10% of the case reports from the CRFs to check the data every 3 months, including logic problems, and test value determination, abnormal safety indicators after treatment, vacancy values, compliance nature, normative, completeness, consistency, etc. All research members in this study will receive professional training before the study. Any corrections or revisions of the protocol will be discussed by the ethics committee of Yueyang Hospital of Integrated Traditional Chinese and Western Medicine. Detailed information of changes will be kept.

### Ethical considerations

The study collects data from patients with NCNP. Informed consent is required from the patients. Patients can terminate participation at any time.

The results of the trial will be shown in tables and figures only, and no individual will be identified. All data collected from this study can only be used for this research. All members of the research team have ethical principles of confidentiality.

In addition, we will try our best to deal with ethical issues which arise during the study. We estimate that the benefits of the study far outweigh any possible risks. The trial has been approved by the ethics committee of Yueyang Hospital of Integrated Traditional Chinese and Western Medicine, which is affiliated with Shanghai University of Traditional Chinese Medicine (2020-018) and registered on ChiCTR (2000036805).

## Discussion

Non-specific chronic neck pain (NCNP) is a common and high prevalence musculoskeletal problem in the world. It can cause ADL, work disability and economic cost, and psychological stress [54, 55]. Because of the high recurrence rate, a scientific and reasonable intervention should be explored and promoted. It can not only relieve symptoms and reduce the burden of individuals and the society, but also decrease the complication and improve the quality of life. Yijinjing and Tuina are important components of traditional Chinese medicine. They have been used for thousands of years to keep people healthy. Quite a few people know the concrete operating procedure, advantages, and efficacy of such interventions. Therefore, the aim of this study is to investigate whether Yijinjing combined with Tuina has any superiority to Tuina.

According to TCM, a healthy human body depends on the coordination of the internal organs and the harmony of qi and blood. The main reason of pain will be attributed to qi stagnation and blood stasis. In this study, relaxing manipulation, clicking on the acupuncture point manipulation, and neck structural rectification are chosen to release adhesion and smooth joint movement so as to alleviate pain and improve joint movement condition. By using these manipulations, the circulation of qi and blood will be promoted. Five movements of Yijnjing which are specifically for the neck are chosen. These movements include neck flexion, rotation, and lateral flexion. The features of Yijijing are the harmony of body, breath, and mind. It puts emphasis on the unity of strength and meditation by using static postures and dynamic movements. It can circulate qi and blood, strengthen the muscles and nourish the tissues and organs, and also arrest spasm [56]. The previous study demonstrated that regular and long-term training of Yijinjing can raise the skeletal muscle strength and improve motor function and ADL [57, 58]. A clinical research reported that after 6 months, Yijinjing multiple factors of depression and anxiety dropped significantly. It indicated that Yijinjing can improve patients’ mental conditions [59].

The present trial is a comparative efficacy of Tuina (control) and Yijinjing combined with Tuina (intervention) for the physical and mental symptoms of NCNP patients. We want to explore whether Yijinjing combined with Tuina is better than Tuina. We will evaluate three aspects of neck pain: pain, physical function, and mental function. we will use validated scales and questionnaires and some measuring instruments to assess the clinical outcomes.

Pain is the most important symptom of neck pain, so visual analog scale (visual analog scale) will be used as the primary outcome. It can evaluate the intensity of neck pain. One of the secondary outcomes is NDI, which can evaluate the limitation of daily life because of NCNP. Cervical active range of motion (AROM) which can evaluate the neck active range of motion is measured by using an easy equipment. SAS can evaluate the anxiety level of patients. Tissue hardness will be measured by a tissue hardness meter and expressed in numbers.

To the best of our knowledge, no study has proved the efficacy of Yijinjing combined with Tuina for patients with NCNP.

High-quality clinical data will be collected because of the rigorous experimental design. The efficacy of this specific intervention protocol for treating NCNP will be evaluated by these data. We hope that this study will provide a solid foundation for the treatment of NCNP, as well as Tuina and Yijinjing research.

### Strengths and limitation of the study

The strength of this trail includes the randomized study design, the pre-defined sample size, and the application of Yijinjing which is designed by an experienced expert. Secondly, the use of standardized measurement instruments will become very important inclusions for the study. Finally, many resistance trainings are limited to equipment-based ones in rehabilitation organizations or hospitals. They cost high and fail to combined positive and passive movement. As a kind of traditional Chinese exercise, it is easy for people to master in a short time. Moreover, Yijinjing does not require expensive equipment. It can not only strengthen the bones and sinews, but also nourish organs. It will make a positive effect on physiological structures and pathological conditions.

There are several limitations to this study. The first is the blinding of the therapist and patients. The nature of the interventions makes it impossible to blind them during the study. Secondly, self-reported results, such as the VAS and SAS, also have limitations because they may be affected by the placebo effect and expected results. Finally, there is in fact no control group. We use Tuina therapy as a control which is considered experimental.

### Trial status

This trial is recruiting patients now. Participant recruitment started in May 2020 and is expected to end in December 2021.

## Data Availability

The authors will submit the research results to a peer-reviewed journal. The data will be put into the China Clinical Trial Registry (http://www.chictr.org.cn). Data and materials can be obtained from the corresponding author after the trial.

## Abbreviations

NCNP: Non-specific chronic neck pain
VAS: Visual analog scale
NDI: Neck Disability Index
SAS: Self-Rating Anxiety Scale
AROM: Active Range of Motion
ROM: Range of motion
EMG: Electromyography
ADL: Activities of daily living
CRF: Case report form
